## Abstract

**Background:**

Radiotherapy (RT) for breast cancer presents a benefit in terms of reducing local recurrence and deaths resulting from breast cancer but it can lead to secondary effects due to the presence of neighboring cardiac normal tissues within the irradiation field. Breast RT has been shown to be associated with long-term increased risk of heart failure, coronary artery disease, myocardial infarction and finally cardiovascular death more than 10 years after RT. However, there is still a lack of knowledge for early cardiotoxicity induced by breast RT that can appear long before the onset of clinically significant cardiac events. Based on a 2-year follow-up prospective cohort of patients treated with breast RT, the BACCARAT (BreAst Cancer and CArdiotoxicity Induced by RAdioTherapy) study aims to enhance knowledge on detection and prediction of early subclinical cardiac dysfunction and lesions induced by breast RT and on biological mechanisms potentially involved, based on functional and anatomical cardiac imaging combined with simultaneous assessment of multiple circulating biomarkers and accurate heart dosimetry.

**Methods/Design:**

BACCARAT study consists in a monocentric prospective cohort study that will finally include 120 women treated with adjuvant 3D CRT for breast cancer, and followed for 2 years after RT. Women aged 50 to 70 years, treated for breast cancer and for whom adjuvant 3D CRT is indicated, without chemotherapy are eligible for the study. Baseline (before RT) and follow-up data include measurements of functional myocardial dysfunction including strain and strain rate based on 2D-speckle tracking echocardiography, anatomical coronary lesions including description of plaques in segments of coronary arteries based on Coronary computed tomography angiography, and a wide panel of circulating biomarkers. The absorbed dose is evaluated for the whole heart and its substructures, in particular the coronary arteries. Analysis on occurrence and evolution of subclinical cardiac lesions and biomarkers will be performed and completed with dose-response relationship. Multivariate model of normal tissue complication probability (NTCP) will also be proposed.

**Discussion:**

Tools and results developed in the BACCARAT study should allow improving prediction and prevention of potential lesions to cardiac normal tissues surrounding tumors and ultimately enhance patients’ care and quality of life.

**Trial registration:**

ClinicalTrials.gov: NCT02605512

## Background

It has been shown that adjuvant Radiotherapy (RT) for breast cancer presents a benefit in terms of reducing local recurrence and deaths resulting from breast cancer [1]. However, breast RT can lead to secondary effects due to the presence of neighboring normal tissues within the irradiation field, including the heart. The severity of radiation-induced toxicity to healthy tissues can unfortunately affect the quality of life of cancer survivors.

### Long term cardiac events

Breast cancer RT irradiation of the heart has been shown to be associated with long-term cardiac toxicity such as heart failure, coronary artery disease, myocardial infarction and finally cardiovascular death more than 10 years after RT with relative risks within the range of 1.2 to 3.5 by comparing left breast treated patients (with higher exposure to heart) to right ones or unexposed ones [1–4]. Moreover, cardiac damage was shown to be correlated with the heart-absorbed dose with 7.4 % rate increase of ischemic heart disease per one Gray (95 % confidence interval, 2.9 to 14.5; *P* < 0.001), with no minimum threshold for risk [4]. Retrospective studies based on records of patients treated with radiation therapy for breast cancer who had undergone a coronary angiography many years after RT, also showed a link between radiation and location of stenosis as stenosis were often present in left anterior descending artery [5–7]. These studies revealed the importance of simultaneous consideration of the location of radiation doses at the structures of the heart combined with localized effects, particularly in the coronary arteries [8, 9]. However, these retrospective studies only considered patients treated until the 90’s that secondarily developed cardiac diseases but didn’t provide information on early signs of cardiotoxicity that can appear long before the onset of these clinically significant cardiac events.

### Subclinical cardiac changes

Long before the onset of clinically significant cardiac events occurring many years after RT, some subclinical cardiac changes can occur over weeks, months or first years after RT, that can be detected either based on functional dysfunction or anatomical modifications measurements.

#### Echocardiography and myocardial changes

Cardiac echography can be used to evaluate myocardial dysfunction. Global Longitudinal Strain and strain rate (GLS) assessed using automated 2D-speckle-tracking echocardiography (STE) is a recent technique for detecting and quantifying subtle disturbances in Left ventricular (LV) systolic function. This technique is operator independent, more reproducible than ejection fraction (EF) and GLS was shown to be a superior predictor of cardiac events compared to EF. In particular, this method was used in the context of cardiotoxicity after breast RT. In Belgium, two prospective studies were based on measurements of strain and strain rate as an indicator of myocardial contractility [10, 11]. Comparing the strain before breast radiation, then a few months later, both studies showed significant changes related to radiotherapy. The most recent study included 51 women treated for left breast cancer and 24 women treated for right breast cancer. Both strain and strain rate were significantly decreased (mean 5 %) during the first year following RT for left-sided patients: a decrease in strain was observed at all post-RT time points (−17.5 ± 1.9 % immediately after RT, −16.6 ± 1.4 % at 8 months and −17.7 ± 1.9 % at 14 months vs −19.4 ± 2.4 % before RT, *p* < 0.01). Similar results for longitudinal strain decrease were also observed in a recent German study [12]. Based on this clinical state, it appeared that early cardiotoxicity of radio-induced breast RT could be measured based on subclinical myocardial functional changes which is concordant with recent publication of recommendations in the evaluation of cardiovascular complications after radiotherapy in adults including in particular cardiac echography examination [13]. However these results on strain and strain rate remain to be confirmed and more precise analyses depending on the dose distribution over the surface of myocardial could enable a better understanding of a possible dose response.

#### CCTA and coronary changes

Coronary computed tomography angiography (CCTA) provides morphological information: visualization of the coronary arteries; visualization of calcification of the coronary arteries and determination of calcium score which reflects the evolution of the coronary disease may help to visually locate vulnerable lipid-rich soft plaques (little or non-calcified) as potential risk of coronary occlusion. By limiting radiation exposure to the phase of interest (generally, the motion sparse diastolic phase), the radiation dose can be reduced, with an average dose < 5 mSv [14]. This CCTA method was used for patients treated with radiation therapy to the chest for Hodgkin lymphoma that developed coronary damages after their RT [15, 16] but even more generally in the follow-up of cardiac patients [17]. Lehman et al. showed the potential of CCTA for accurate monitoring of the progression of calcified and non-calcified plaques from a population of 69 patients with chest pain examined twice at 2-year intervals [17]. From tracking nearly 9000 segments of coronary arteries in the cohort, a significant 12.7 % increase in the mean number of cross-sections containing any plaque was observed (*p* = 0.01). While this study did not consider radiation exposure of the heart, it does illustrate that the CCTA could be used for monitoring short-term changes in coronary changes. No study focused on women treated with breast radiotherapy while CCTA has a potential to detect the onset or progression of early coronary changes due to irradiation.

### Circulating biomarkers

From a biological point a view, understanding the biological mechanism of the initiation and progression of early radiotherapy side effects on normal tissue such as cardiac tissue is also an important issue. To our knowledge, there are no specific and early biomarkers of radiation-induced heart damage at the present time. According to the dose distributions at heart, ionizing radiation can generate cardiac injury and a major challenge remains the identification of reliable biomarkers that could help to diagnose and predict cardiotoxicity. Depending on the type of injuries (microvascular rarefactions, coronary damage, tissue inflammation) potentially relevant biomarkers are different.

Many classical biomarkers (*C-reactive protein*, *N-terminal pro-B–type natriuretic peptide* (NT-proBNP) and *troponin* (TnI), *…*) were shown to be potential biomarkers for cardiac damage, in particular after radiotherapy [18–20]. Circulating inflammatory cytokins [21] can also sign tissue inflammation. It was also showed that irradiation induces acute endothelial activation or dysfunction that can be observed many weeks after irradiation and resulting in pro-inflammatory endothelial phenotype.

Another hypothesis to explore is that the irradiation may be responsible for an increase in the circulating levels of certain miRNAs expressed by cells of the heart tissue Currently, the potential function of extracellular miRNAs is being studied intensively, and the first studies have confirmed that miRNAs may indeed function in cell-to-cell communication. [22]. Many studies have reported the use of miRNAs as circulating biomarkers for diagnosis or prognosis of cardiovascular diseases. Although many of those studies still require replication in multiple independent study populations, the picture emerges that some plasma miRNAs are quite specific for cardiovascular pathologies and may be useful for diagnostic and monitoring purposes.

The complex and multifactorial nature of atherogenesis and development of atherothrombotic complications involves numerous interactions between various cell types inside the vascular wall (e.g., macrophages and smooth muscle cells) and in the blood (e.g., leukocytes and platelets). One relatively recent advance in this area is the discovery of circulating microparticles. High levels of circulating microparticles found in many cardiovascular diseases demonstrate the importance of platelet, monocyte and endothelial activation and could condition remote sustainability illnesses [23].

Based on this state of art, the simultaneous assessment of multiple biomarkers may be of strong interest for RT cardiotoxicity.

### Cardiac radiation exposure

Considering the dosimetric point of view is also important to quantify precisely the risk of cardiac lesion. As awareness of radiotherapy cardiotoxicity has grown and technology has developed, in the history of breast cancer RT regimens, the range of doses to the heart has changed over the past few decades [24–26]. Mean heart dose decreased from more than 5Gy in the 50’s to less 3 Gy in the last decade [27] and availability of 3-dimensional CT planning (3D CRT) in the 90’s has enabled clinicians to reduce normal tissue doses generally.

Routinely, whole heart dose-volume histograms (DVH) are available based on radiotherapy simulation CT scans. However these DVH cannot provide information on the location of higher doses. Highest cardiac radiation doses can be observed in the apex and the apical-anterior segment and some hot spots > 50Gy persist in some parts of the heart [12] which may still today induce cardiac lesions, in particular for coronaries [28]. To avoid damage and complications to healthy tissues, dose constraints are applied to the organs at risk. The QUANTEC - Quantitative Analysis of Normal Tissue Effects in the Clinic- recommendations, specify that the heart should always be contoured and less than 10 % of the heart must receive more than 25 Gy: "For partial irradiation, a conservative model-based estimates predict that a V25Gy < 10 % (in 2 Gy per fraction) will be associated with a <1 % probability of cardiac mortality 15 years after RT." [29]. However, no dose recommendation exists for the coronary arteries whereas calculated mean heart doses highly differ from mean coronary arteries doses due to important dose gradient. In clinical practice, coronary arteries are not contoured. The specific relationships between doses to cardiac structures and subsequent toxicity have not been well defined. As a consequence, studies based on radiation dosimetry that is able to take account of the distribution of dose within the heart (rather than just the mean heart dose) may provide further insight into the spatial location of heart damages in breast cancer RT [28]. Precise approach of heart substructure dosimetry has been developed at IRSN for Hodgkin patients by merging RT simulation CT scans and CCTAs to obtain detailed cardiovascular anatomies and finally radiation treatment parameters were used to estimate CA radiation doses [30]. Similar approach could be used for breast cancer radiotherapy.

### NTCP models

The relationship between dosimetry data and toxicity to healthy tissue is a key element in the ability to calculate risk. Mathematical models have been developed in recent years with the aim of using dosimetric data (mainly DVH) to estimate a complication probability (mainly a clinical sign): the NTCP models (Normal Tissue Complication Probability). Research on parameters to optimize the NTCP models (physical, imaging, dosimetry, clinical) are a major challenge to improve knowledge on the relationship between a received dose and toxicity to healthy tissue [31, 32]. In addition, the enrichment with biological data of these models is a fundamental NTCP track in the overall goal of optimizing risk prediction. In the context of cardiotoxicity, this type of model has been poorly exploited [33], due to the long lag time to see the clinical signs and the fact that toxicity evaluation criteria is limited primarily to acute effects, but rarely to the late effects that develop after several years. By defining a short term subclinical cardiotoxicity, it would nevertheless be possible to apply these methods to know predictors of subclinical complications and ultimately to predict the risk of subclinical complication itself predictive of clinically significant complication that would occur several years later.

## Methods/Design

### Study objectives

#### General aim

Based on a 2-year follow-up prospective cohort of patients treated with breast radiotherapy (3D CRT), the BACCARAT study aims to enhance knowledge on detection and prediction of early subclinical cardiac dysfunction and lesions induced by breast cancer radiotherapy and on biological mechanisms potentially involved, based on functional and anatomical cardiac imaging combined with simultaneous assessment of multiple circulating biomarkers and accurate heart dosimetry.

#### The primary objective is:

I.To evaluate the occurrence and evolution of subclinical cardiac lesions at myocardial levels (measure of myocardial contractility - strain) and coronary levels (measure of coronary plaque index) based on cardiac imaging techniques (cardiac ultrasound exam"2D strain" and CCTA).

#### The secondary objectives are:

II.Study of the temporal variations of a panel of targeted circulating biomarkers of microvascular rarefactions, coronary damage, and tissue inflammation related with breast RT.III.Evaluate precisely the absorbed doses, for the whole heart and for the different structures of the heart, specifically the coronary arteries.IV.Analyse the dose-response relationship between subclinical cardiac changes, biomarkers, and absorbed doses and propose multivariate model of normal tissue complication probability (NTCP), which takes into account relationships among all these parameters and potentially offer a powerful approach to the optimization of risk assessment.V.Establish a biobank of plasma for further analysis of biomarkers linked to the study of RT cardiotoxicity.

### Study design and population

BACCARAT study consists in a monocentric prospective cohort study that will finally include 120 women treated with adjuvant 3D CRT for unilateral breast cancer in the Clinique Pasteur in Toulouse, France, without chemotherapy, and followed for 2 years after RT.

In the Clinique Pasteur, there are no competing methods to 3D-CRT at the moment. All patients with breast cancer are treated with 3D-CRT and breath-hold gating is used for patients treated left breast cancer with heart very close to the anterior chest wall or for dose constraints achievement (mean heart dose < 5Gy and V25Gy < 10 %). Women aged between 50 and 70 years, for whom adjuvant 3D CRT is indicated with or without breath-hold gating, with no indication of chemotherapy are eligible for the study. Both women with left (80 % of the sample) or right (20 % of the sample) breast cancer are included. This choice to include both sides is justified by two reasons: (i) if the internal mammary chain is treated significant doses can result, whatever the treated side; (ii) if the internal mammary chain is not treated the right side treatment will provide lower doses, an important point for the dose response analysis. With this design, each patient (after RT) could be her own control (before RT). Moreover, the left-sided patients could also be compared to the right-sided patients. Inclusion and exclusion criteria are presented in Table 1.

**Table 1 Tab1:** Inclusion and exclusion criteria

Inclusion criteria	Exclusion criteria
• Age between 50 and 70 years • Women surgically treated for left or right breast cancer and for whom adjuvant treatment is radiotherapy with irradiation of the breast or chest wall irradiation and possibly ganglion chains, • Adjuvant radiotherapy with 3D CRT performed in Clinique Pasteur Toulouse • WHO performance status ECOG (Eastern Cooperative Oncology Group - index usually used to describe the patient's condition) = 0 or 1 • Being volunteer to participate in the study and having signed the consent form	• Indication of adjuvant chemotherapy • Clinically or radiologically detectable metastasis • Personal history of coronary artery disease or myocardial disease • Personal history of breast cancer or other cancer requiring radiotherapy to the thorax • Patient with controlled infection or severe disease and/or non-hazardous to their participation in the study • Contraindications to injection of iodinated contrast (for CCTA): pregnancy, renal failure, allergy • Pregnancy, lactation • Abnormal echocardiography before radiotherapy: - LVEF <50 % - Longitudinal strain > − 16 % - Longitudinal strain rate <1 %/s - Abnormal wall motion • CCTA before radiotherapy showing that therapeutic management is required (by decision of the radiologist and cardiologist)

*3D CRT* 3D conformal radiation therapy, *WHO* World Health Organisation, *CCTA* coronary computed tomography angiography, *LVEF* left ventricular ejection fraction

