**Fig. 2 Fig2:**
[figure not shown]
15 segments of coronary arteries. LM: Left main coronary artery; LAD: left anterior descending artery; LCX: left cicumflex artery; RCA: right coronary artery. For each segment, the following index are measures: stenosis in % narrowed; presence of calcification; presence of soft plaque (adapted from [41])

**Table 3 Tab3:** List of circulating biomarkers measured in BACCARAT protocol

Classical biomarkers of cardiac injury
C-reactive protein, Troponin I, B-type natriuretic peptide (NT-Pro BNP), beta2-Microglobulin, Galectin 3
Inflammatory cytokines:
Interleukin 6, Interleukin 8, Interleukin 18, TNF-α
Endothelial activation and dysfunction
sVCAM,-1, s-ICAM-1, E-selectin, P-selectin, vWF, PAI-1, Fibrinogen, Thrombomoduline, TGF-β1
Microparticles
CD14(monocytes), CD31(endothelial), CD41(platelets), CD3(lymphocyte), CD235a (erythrocyte)
microRNAs
miR-1, miR-133, miR-208, miR-499, miR-126, miR-130, miR-145, miR-181, miR-150, miR-155, miR-223, miR-17, miR-18, miR-22, miR-34, miR-92, miR-140, miR-182, miR-199, miR-423, miR-590.

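### One exclusion criterion in Table 1 has its qualifiers reversed: as written it excludes controlled infection and non-hazardous conditions, and does not exclude uncontrolled infection

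*Protocol article*

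**What the plan says.** The section Study design and population of the protocol article refers the reader to Table 1 for eligibility: "Inclusion and exclusion criteria are presented in Table 1". In the exclusion column of that table stands "Patient with controlled infection or severe disease and/or non-hazardous to their participation in the study".

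The bullet immediately before it is "Personal history of breast cancer or other cancer requiring radiotherapy to the thorax" and the bullet immediately after it is "Contraindications to injection of iodinated contrast (for CCTA): pregnancy, renal failure, allergy". Both name an unfavourable state as the reason for exclusion.

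The only general-health requirement in the inclusion column is "WHO performance status ECOG" of 0 or 1, which does not mention infection or comorbidity.

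Table 3 lists the circulating biomarkers, among them "Interleukin 6, Interleukin 8, Interleukin 18, TNF-α". Under Study procedures, blood is drawn before radiotherapy, at its end, at six months and at two years. Under Planned analysis, the pre-radiotherapy values serve as the reference and changes are tested with paired Wilcoxon tests.

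**The concern.** An exclusion list works by naming states that make a woman unsuitable. This bullet names states that sound acceptable: an infection under control, and a condition that carries no hazard for taking part. Whoever applies it as written would exclude the women with those states, and would find nothing in the bullet to exclude a woman whose infection is not controlled.

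Two things are at stake. The first is the safety purpose of the line: it is the only bullet that addresses infection, and the only one that refers to hazard from participation in general terms. The second is the biomarker analysis. Objective II compares each woman with her own pre-radiotherapy sample, and several of the markers measure inflammation or the acute-phase response. An infection that is active at the baseline draw and has resolved later would enter her change score directly.

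**Working it through.** No sample-size or power arithmetic applies. The check has four parts.

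**1. Placement.** Table 1 was flattened when the text was read from PDF, so the column has to be confirmed. The bullet comes after the column break that follows the consent item, and it lies between two evident exclusions (prior cancer needing thoracic radiotherapy, and contrast contraindications). It is in the exclusion column. The sentence is unbroken and both qualifiers are complete words, so extraction damage or redaction is an unlikely explanation.

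**2. Literal meaning.** The sentence can be parsed in two ways. Under reading A, the word controlled governs both infection and severe disease. Under reading B, it governs infection only, and severe disease stands alone.

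| State at screening | Excluded by this bullet, reading A | Excluded by this bullet, reading B |
|---|---|---|
| Controlled infection | yes | yes |
| Condition not hazardous to participation | yes | yes |
| Uncontrolled infection, hazardous to participation | no | no, unless it counts as severe disease |
| Severe disease, uncontrolled and hazardous | no | yes |

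The first two rows are the reverse of what an exclusion is for. The third shows that the bullet does not exclude uncontrolled infection as such; the *or* in its last limb could catch one that is judged non-hazardous, which only repeats the reversal. The fourth row depends on the parsing, so nothing firm can be said about severe disease.

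**3. Correction elsewhere.** The Abstract and the body of Study design and population give age, adjuvant 3D CRT, no chemotherapy and tumour side. Sample size calculation mentions exclusions for abnormal baseline imaging and for later cardiotoxic chemotherapy. None of these restates or repairs the infection bullet.

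**4. Reach into the analysis.** The count of markers in Table 3 is:

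- classical: 5
- cytokines: 4
- endothelial: 9
- microparticles: 5
- microRNAs: 21
- total: 5 + 4 + 9 + 5 + 21 = 44

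At least six are inflammatory or acute-phase markers: C-reactive protein, interleukins 6, 8 and 18, TNF-alpha and fibrinogen. That is 6/44 = 13.6 %.

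For one woman and one marker, write the change as D(t) = Y(t) − Y(0), with Y(0) the pre-radiotherapy value and t the end of radiotherapy, six months or 24 months. If an infection at baseline raises Y(0) by δ and has gone by time t, the recorded change is D(t) − δ. The same δ enters all three comparisons and can mask a rise due to radiotherapy. The documents give neither δ nor the share of women with an active infection at baseline, so the size of any bias cannot be computed.

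**The case against.** The best case on the other side is that this is an evident slip in a condensed article. Nobody would deliberately exclude women because their condition is non-hazardous. The article has similar slips: Sample size calculation labels a value given per second as strain when it must be strain rate, and Table 2 lists radial strain rate twice. The study has ethics and agency approval, the approved protocol and the screening form are not shown, and staff may well have applied the intended sense.

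Most of this stands, and it limits the consequences. It does not remove the error: the line is an operative eligibility rule, stated in a sense that defeats its function, and nothing in the article corrects it.

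A reader might also infer that the trial gives no protection to women for whom participation is hazardous. The documents do not support that. Table 1 separately excludes contrast contraindications, metastasis, previous coronary or myocardial disease, pregnancy and lactation, abnormal baseline echocardiography, and baseline CCTA findings that need management. It also requires performance status 0 or 1, and Study procedures adds a baseline cardiology consultation. The hazard of the contrast scan in particular is addressed by its own bullet. Nor does it follow that every woman with a hazardous condition passes this bullet, since under reading B severe disease is excluded outright.

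**Conclusion.** The bullet is wrong as written. Its qualifiers contradict its place in the exclusion column, and it fails to exclude uncontrolled infection. Its effect on severe disease is ambiguous.

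The supported consequence is modest: the safety purpose of this one line fails, and the baseline reference values of at least 6 of 44 biomarkers in secondary objective II could be distorted. That second consequence assumes that the line was applied literally and that some woman otherwise eligible had an active infection at the baseline draw. The documents establish neither.

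It would go too far to conclude that women were wrongly enrolled or wrongly turned away, because nothing shows that the reversed wording was used at screening. No effect on strain, coronary plaque, the sample size of 120 or the choice of tests is shown. The point merits correction because it concerns eligibility and the remedy is small.

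**What to change.** Compare this line with the ethics-approved protocol and with the screening form, and correct Table 1 so that the wording agrees with its function as an exclusion. The correction should also settle whether severe disease is excluded in itself or only when qualified. The content of the clinical rule is for the sponsor to confirm from the approved text; this review does not propose one.

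If only the article is wrong, a one-line correction suffices. Only if an operational document carries the reversed wording should that document be corrected too and the women already screened be checked against the intended rule. Status of the study says that recruitment is under way, so in that case the check should not wait.

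The cost is one corrected line, a comparison of documents and, conditionally, a look through the screening records. No further patients, visits or procedures are needed.
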